**Other measures**		
Age	Years	t1
Gender	Female/male	t1
Height	Centimetres	t1
Weight	Kilo	t1
Marital status	Living alone or not	t1
Employment status	Working full time/working part time/not working/student/working full time in the home/unemployed or seeking work/age retired/disability pension/sick leave	t1
Level of education	7-10 years of education, 10–12 years of education, more than 12 years of education	t1
Comorbidity	Presence of 16 diseases/health problems (yes/no)	t1
Level of exercising	3 times pr week, 1–2 times pr week, 1–2 times pr month, not on a regular basis, or I can not exercise or be social active due to functional limitations	t1
Physical and social activity	3 times pr week, 1–2 times pr week, 1–2 times pr month, not on a regular basis, or I can not exercise or be social active due to functional limitations	t1, t2, t3, t4
Physical activity	International Physical Activity Questionnaire-Short Form, IPAQ, mean minutes/week of, vigorous-intensity activity, moderate-intensity activity, walking, and sitting	t1, t2, t3, t4
Illness perception	Rheumatic Disease Illness Perception Questionnaire, 1 to 5, 1 is “not at all”	t1, t2, t3, t4

t1 = admission to rehabilitation, t2 = discharge from rehabilitation, t3 = six months after rehabilitation, t4 = twelve months after rehabilitation.

The data at the six- and 12-month follow up will be collected in telephone interviews by secretaries working at the National Resource Centre for Rehabilitation in Rheumatology. Two weeks before each interview, the questionnaires will be sent by post to the participant, together with a letter containing a suggested time for the interview and a request that the participant may read through- and complete the questionnaires on the last day before the interview. Contact information will be provided in the letter, and the participant will be encouraged to contact the secretary to make a new appointment if he/she is not available at the suggested time.

#### Primary outcome measure

The primary outcome in this study will be goal attainment and health-related quality of life measured by the Patient Generated Index (PGI)
[42,43], which is an individualized instrument completed in three stages: In stage 1, the respondent will be asked to list up to five areas of life affected by his/her rheumatic condition, with an example list of areas provided that he/she can consult if necessary. A predefined sixth area will be listed as “all other areas of your life affected by your rheumatic disease”. In stage 2, the respondent will rate the areas given in stage 1 on numeric rating scales ranging from 0–6 where 0 = “as bad as could possibly be” and 6 = “as good as could possibly be”. In stage 3, the respondent will distribute 10 points to indicate the relative importance of each of the areas described in stage 1, with the most points allocated to the most important areas.

A summarized index score of PGI will be generated as follows: Each area ratings from stage 2 will be multiplied by the points given to the area in stage 3. Thereafter, the product of all areas will be summed up and divided by the number of areas (normally six including the predefined area). Lastly, this sum will be multiplied by 10 to yield a PGI index score between 0 and 100, with higher scores reflecting a better health-related quality of life.

At follow-up after six and twelve months, participants will be asked to score the same five areas that they listed in stage 1 at baseline.

In this study, the baseline PGI areas will also serve as a basis for developing individual rehabilitation goals for patients in the intervention group and for evaluating goal attainment.

The psychometric properties of the Norwegian version of the PGI has recently been tested with good results in patients with rheumatic diseases undergoing rehabilitation
[39].

#### Cost-effectiveness

The direct and indirect costs in the study period will be self-reported at six and 12 months as the number of days of sick leave and absence from paid work over the past six months, the number of visits to a given list of health providers during the past six months and the number of hospital visits or stays over the past six months. The participants will also report on any medication taken for their rheumatic disease, medical or technical equipment purchased during the past six months and the number of days or hours they needed paid or unpaid help from others, including any costs related to paid help.

Additionally, data on health-care resource allocation and costs related to the rehabilitation stay will be collected at all centres. This will include recordings of the time used on the goal-setting conversations at admission and discharge, on the four follow-up calls, and on training of the involved personnel.

An important way of assessing the effects of treatment in health economic evaluations is the use of utility indexes, and in this study we will use the SF6D utility index as a utility measure in the cost-effectiveness analyses. SF6D is comprised of 11 items from the SF-36
[44] that are transformed into a continuous outcome scored on a 0.29–1.00 scale, with 1.00 indicating full health
[49].

#### Other measurements

All participants will be asked to fill in a questionnaire at inclusion containing information on socio-demographics (age, gender, height, weight, marital status, employment and level of education), whereas comorbidity will be reported by asking the participant to check off the presence of 16 diseases/health problems (yes/no).

The level of exercising and social activity will be self-reported using two scales with the following response categories: “3 times per week”, “1-2 times per week”, “1-2 times per month”, “not on a regular basis” and “I cannot exercise or be socially active due to functional limitations”.

The level of physical activity will be self-reported using the International Physical Activity Questionnaire-Short Form, (IPAQ-SF), which is expressed as weekly energy expenditures determined by the expressed metabolic equivalent task minutes per week (METs min/wk) of different categories (sitting, walking, moderate- and vigorous-intensity physical activity and total physical activity score) and physical activity levels (low, moderate, and high)
[50].

Illness perception will be captured by the Rheumatic Disease Illness Perception Questionnaire (RD-IPQ)
[51], which is adapted for patients with rheumatic diseases from the original IPQ
[52] and contains 11 questions about illness perceptions over the past two weeks, with five response alternatives ranging from “not at all” to “to a very large extent”. An overall scale of illness perceptions will be computed by adding the items representing illness consequences, illness emotions and illness identity. In a last open question, participants will be asked to write down any thoughts concerning the cause of their rheumatic disease.

### Text analyses

The content and stability of rehabilitation goals will be explored by text analyses, and the raw text materials for coding will be the rehabilitation goals agreed upon by the participants and health professionals during the semi-structured interviews shortly after admission, at discharge and in the follow-up telephone calls (see outline of questions to be asked in the interviews in Table 
2).

The biostatistician will draw a random sample of approximately 25% of the participants from the total sample, stratified by centre and diagnosis.

A first analysis will be carried out separately by two independent researchers, who will read through the goal descriptions to identify and code statements concerning patients’ long- and short-term goals. Following this, the codes will be combined into broader categories, and finally into overarching themes
[53]. Thereafter, the analyses will be compared and discussed until an agreement is reached, and if applicable, taxonomies for categorizing health and functioning such as the International Classification of Function, Disability and Health (ICF) will be used as a framework for the analyses
[54]. Furthermore, goals agreed upon shortly before discharge or in the follow-up period will be compared to the initial goals to help explore whether goals are changing over time, and if there are trends or patterns that characterize such changes.

All variables will be entered into the model and the best subsets of prognostic factors will be selected by excluding those independent variables with the smallest contribution to the model (i.e. those with the largest P-value). The model will be adjusted at every step for the baseline value of the outcome and the other independent variables.

The primary economic evaluation will take the form of a cost-effectiveness study of the cost per extra quality adjusted life years (QALYs), which will be calculated using the SF6D scores at six and 12 months, respectively. Differences in mean change from the baseline for the SF6D to each time point will be weighted by the time from the baseline using generalized linear regression modeling, adjusting for baseline levels of the SF6D to construct QALYs and then compared between groups.

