## Background

Inflammatory rheumatic diseases are characterized by inflammatory processes that may lead to joint damage and various degrees of disability, thus representing a major burden to the individual patient and society. Current treatment focuses on early diagnosis and early use of disease modifying agents. Nevertheless, a major percentage of patients has a residual disability and will need some form of rehabilitation throughout their life
[1].

Rehabilitation has been defined by the World Health Organization as “a process aimed at enabling people with disabilities to reach and maintain their optimal physical, sensory, intellectual, psychological and social functional levels. Rehabilitation provides disabled people with the tools they need to attain independence and self-determination”
[2].

As such, the rehabilitation process involves several professions and services, and is characterized by being tailored to the patients’ individual needs and challenges, with the aim of reducing the consequences of illness while improving activity, participation and quality of life
[3].

Several studies have shown that patients with rheumatic diseases benefit from rehabilitation. However, the effect seems to fade over time, and most patients are back to their initial health status six to 12 months after discharge
[4-7]. A major challenge is therefore to help patients maintain self-management strategies introduced in the rehabilitation period, thereby enhancing a longer lasting effect of rehabilitation.

Goal planning is considered as an essential part of rehabilitation practice and is a process directed at setting goals at various levels of function, within different life areas and in various time frames
[8]. The key components of goal setting are comprised of goal identification and negotiation, action planning and appraisal and feedback of performance
[9,10], and individualized weekly action plans and participant handbooks are recommended to enhance participants’ adherence and progress towards long-term goals
[11]. Even though research concerning the effectiveness of goal planning in clinical rehabilitation is scarce, the conclusions in a systematic review by Levack et al. are that there is some, though limited, evidence that goal planning can influence patient adherence to treatment regimes, as well as strong evidence that specific, challenging goals can improve immediate patient performance in some specific clinical contexts

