### Study design

This will be a pragmatic, multicentre, stepped-wedge cluster randomized controlled trial
[37,38] in which participants will be assessed at admission to- (baseline) and discharge from a rehabilitation stay, and after six and 12 months (Trial registration: ISRCTN91433175).In the trial, six participating centres (clusters) will switch from the control- (the current rehabilitation programme) to the intervention phase (a new rehabilitation programme with structured goal planning and tailored follow-up added to the existing programme) in a randomized order (see Figure 
1 for an outline of the study design). All centres will start the trial simultaneously and act as controls until the point in time that they are randomized to cross over from control to intervention, and all centres will provide the new programme by the end of the inclusion period.

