**Cost-effectiveness:**		
Utility	SF6D utility index, 0.29–1.00, 1.00 is full health	t1, t2, t3, t4,
Sick leave and absence from work past six months	Number of days	t3, t4,
Health care utilisation past six months	Number of visits and/or hospital stays	t3, t4,
Use of medication	Name and dosage of medicine	t1, t2, t3, t4,
Medical or technical equipment past six months	Type and costs of equipment purchased	t3, t4,
Paid and unpaid help past six months	Costs and number of days and hours,	t3, t4,
Costs related to the rehabilitation stay	Costs pr day at each rehabilitation centre x number of days	t2

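### The stated rule for building QALYs, weighting each SF6D change by its time from baseline, does not give the area under the utility curve on any literal reading

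*Protocol article*

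**What the plan says.** The Protocol article (Statistical analyses) makes cost per additional QALY the primary economic evaluation. The QALYs come from the SF6D, "which will be calculated using the SF6D scores at six and 12 months, respectively". The construction is then stated: "Differences in mean change from the baseline for the SF6D to each time point will be weighted by the time from the baseline", by generalized linear regression, "adjusting for baseline levels of the SF6D to construct QALYs and then compared between groups".

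Baseline is admission: "participants will be assessed at admission to- (baseline) and discharge from a rehabilitation stay" (Study design). The follow-ups are counted from the end of the stay: "t3 = six months after rehabilitation, t4 = twelve months after rehabilitation" (footnote to Table 3). Table 3 lists the utility measure as "SF6D utility index, 0.29–1.00, 1.00 is full health", collected at all four time points including discharge. The article does not mention area under the curve, interpolation or interval length, and nothing elsewhere in it modifies the weighting sentence.

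**The concern.** A QALY is utility accumulated over time. A measurement therefore counts in proportion to the lengths of the intervals it borders, not its distance from the start. The 12-month score borders one half-year interval and the six-month score borders two, so the 12-month change should carry half the weight of the six-month change. Weighting by time from baseline gives the later change the larger multiplier.

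The QALY difference is the denominator of the primary economic result, and cost-effectiveness is part of the main objective with its own research question. An analyst who followed the sentence as written would put the wrong quantity in that denominator. The article does more than leave out a formula: it states a weighting rule, and the rule as worded is not the area.

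**Working it through.** **Inputs.** Time points 0, 0.5 and 1 year and the weighting rule come from Statistical analyses. The change at baseline is 0 by definition. The between-group differences d6 and d12 are not in the article; the values below are assumptions, from −0.02 to 0.04. The article states no QALY figure, so there is none to reproduce.

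**Area under the curve, straight lines between assessments**
- 0 to 6 months: 0.5 × (0 + d6)/2 = 0.25×d6
- 6 to 12 months: 0.5 × (d6 + d12)/2 = 0.25×d6 + 0.25×d12
- One-year total: 0.5×d6 + 0.25×d12

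**The stated rule, read three ways**
- Summed: 0.5×d6 + 1.0×d12. Subtracting the area leaves an error of 0.75×d12, which is zero only if d12 = 0.
- Normalised to sum to one: (0.5×d6 + 1.0×d12)/1.5 = d6/3 + 2×d12/3. The area's relative weights are 0.5/0.75 = 2/3 and 0.25/0.75 = 1/3, so the order is reversed.
- Separate horizons: 0.5×d6 at six months, where the area is 0.25×d6; and 1.0×d12 at 12 months, where the area is 0.5×d6 + 0.25×d12. Each product treats the change at the end of the horizon as present in full from baseline.

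**Illustrations over one year (assumed differences)**

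| d6 / d12 | Area | Summed | Normalised | 12-month product alone |
|---|---|---|---|---|
| 0.04 / 0.04 | 0.030 | 0.060 | 0.040 | 0.040 |
| 0.04 / 0.02 | 0.025 | 0.040 | 0.027 | 0.020 |
| 0.02 / 0.04 | 0.020 | 0.050 | 0.033 | 0.040 |
| 0.04 / 0 | 0.020 | 0.020 | 0.013 | 0 |
| 0.04 / −0.02 | 0.015 | 0 | 0 | −0.020 |

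In the first row the summed rule doubles the QALY gain (0.060/0.030 = 2.0), so for a given incremental cost the cost per QALY is halved.

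**Does the length of stay matter?** Baseline is admission while follow-up runs from discharge, and Table 1 gives stays from six days to four weeks. Let s be the stay in years (6/365 to 28/365).
- Stated rule, ratio of 12-month to six-month weight: (1 + s)/(0.5 + s) = 1.97 to 1.87.
- Area: the six-month weight is 0.5 + s/2 = 0.508 to 0.538 and the 12-month weight is 0.25, a ratio of 0.49 to 0.46.
- If the discharge score is included, the area weights are 0.25 + s/2 = 0.26 to 0.29 on the discharge change, 0.50 on d6 and 0.25 on d12.

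The contrast between the rule and the area is essentially unchanged.

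**The case against.** The strongest objection is that the sentence is condensed prose, not a formula. It gives no numerical weights, and an author might describe an ordinary area calculation as time-weighting the utility changes. The full protocol and any analysis plan, where the formula would normally stand, are not shown. This has force: it cannot be said that the trial will compute the wrong quantity. What remains is that the wording names the weight as time from baseline, and none of the three literal readings reproduces the area in general.

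A reader might infer that the 12-month change definitely counts double. That holds only if the two changes are combined. If the six- and 12-month results are separate horizons, there is no relative weight to reverse, and the fault is the different one shown above.

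A reader might also think the error is worst because benefit is expected to fade, citing Background: "the effect seems to fade over time, and most patients are back to their initial health status six to 12 months after discharge". That sentence describes patients' own course under existing rehabilitation, not the difference between the two programmes. The new programme is meant to preserve gains after discharge (Background; Intervention group), so a sustained difference is the case it aims for. Under the summed reading, full fading to 0.04/0 produces no error at all, whereas the sustained case is out by a factor of two.

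Finally, the PGI primary outcome, sample size, randomisation and data collection are untouched, and the SF6D data needed for a correct calculation are being collected. That limits the seriousness but does not remove the point.

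**Conclusion.** The point holds as a fault in the stated rule: followed literally, it does not give the area under the SF6D curve, and nothing else in the article corrects it. The weight comparison assumes only straight lines between assessments.

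The size and direction of any error cannot be established from the article, because they depend on d6 and d12. On the summed reading the error is 0.75×d12: it overstates the gain when the 12-month difference favours the new programme, understates it when that difference is negative, and is nil when that difference is zero. On the separate-horizon reading, an effect that fades fully by 12 months would show no gain at 12 months against an area of 0.020 (assumed 0.04/0), leaving cost per QALY undefined.

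This should be fixed before the economic analysis. Confidence is moderate, because the sentence may be a loose description of the correct method.

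**What to change.** Replace the weighting sentence with an explicit definition: QALYs are the area under the SF6D curve, that is, the sum over intervals between assessments of the interval length in years times the mean of the SF6D values at its two ends, compared between groups with adjustment for baseline SF6D. State which assessments enter, and whether the result is one 12-month QALY or one per horizon.

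The definition should not drop everyone who misses a visit, since Sample size calculations allows for 20% drop-out. There are two workable routes:
- Keep the planned regression, estimate the adjusted differences at each follow-up, and combine them with interval-based weights: 0.5 on the six-month and 0.25 on the 12-month difference if only those two follow-ups are used.
- Compute individual areas after the trial's missing-data handling has been applied.

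The cost is a sentence or two in the protocol or analysis plan. No new data are needed, and the clinical analyses do not change.

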### Ethical considerations

The study has been approved by the Norwegian Regional Committee for Medical Research Ethics (REK South-East, 2011/909) and by the Norwegian Social Science Data Services (2011/6602).

The research will be carried out in compliance with the Helsinki Declaration, personal confidentiality will be guaranteed and declarations of voluntary participation with detailed information on the study purposes and processes will be signed by each participant, thereby emphasizing the right to withdraw from the study at any time without any explanation.

The randomization procedure is deemed as being ethically acceptable because all participants will receive a rehabilitation stay comprised of either the rehabilitation programme currently provided at the participating centres or the new and potentially more effective programme. Hence, no participants will receive an intervention that is below the standard currently delivered at each centre.

## Discussion

Comprehensive rehabilitation, involving health professionals from various disciplines, is widely used as an adjunct to pharmacological and surgical treatment in people with rheumatic diseases. However, the evidence for the clinical- and cost-effectiveness of such interventions is limited
[57].

This paper outlines the protocol for a study where the main aim will be to assess the effects of a structured goal planning and tailored follow-up programme in rehabilitation for patients with rheumatic diseases, using a multicentre, stepped-wedge randomized controlled design.

According to Brown et al.
[37], two key conditions should be met in order to select the stepped-wedge design over a traditional parallel design: 1) There should be a prior belief that the intervention will do more good than harm, 2) There should be practical, logistical or financial constraints, which means that the intervention can only be implemented in stages. Both these conditions will be met in our study. Concerning the last condition, there would be a risk for contamination between two parallel groups localized at one institution in a traditional RCT because the patients in the groups might exchange information and experiences, thereby possibly diminishing the differences between the two intervention programmes. The stepped-wedge design protects against such contaminant effects.

Furthermore, all participants in the trial will receive rehabilitation, regardless of group allocation. This may reduce the chance that participants refuse participation for fear of ending up in a control group with an inferior treatment. The design may therefore increase the inclusion rate, and also to a large degree keep participants blinded for group allocation.

Based on current knowledge and evidence, we will develop a new rehabilitation programme that includes structured goal planning and tailored follow-up after discharge. The main objective of the study will be to evaluate goal attainment, health effects and the cost-effectiveness of this new programme compared to current traditional rehabilitation programmes. We will seek to include a minimum of 312 participants from six rehabilitation centres, which will make this one of the largest rehabilitation studies conducted within this patient population. The findings will therefore constitute an important contribution to more cost-effective- and evidence-based rehabilitation services for people with rheumatic diseases.

In a review of the efficacy of multidisciplinary team care programmes in rheumatoid arthritis, Vliet Vlieland et al. advocate the use of patient-oriented outcome measures and procedures to help enhance the role of the patient in the team care process and communication among health professionals
[58]. The primary outcome in this study will be the Patient Generated Index (PGI), which is a patient-specific measure of a health-related quality of life that allows each patient to choose and rate the domains that he/she consider important.

Because the PGI captures the aspects of life that are of direct concern to the individual, the “noise” that is present in standardized instruments will be reduced, which in theory will have the potential to make it more responsive to capture the effects of rehabilitation
[43]. In addition, the described domains may be used as a basis for discussing long- and short term rehabilitation goals, thus enhancing communication and an active role for the patient in the rehabilitation process.

A possible limitation in the PGI is that participants will select and score those areas of life that are experienced as problematic at baseline. The scores may therefore be prone to regression to the mean. As this probably will occur in both groups, it will, however, not affect the effect estimate, calculated as the differences between groups.

In this trial, we will also use the SF-36 as a standardised generic measure of health related quality of life. The combination of a patient-specific measure and a questionnaire with standardised items may ensure that different of aspects of health related quality of life are captured, and will also allow for comparison of populations and results across studies.

Regarding scientific benefits, the multicentre design will ensure that the new programme will be implemented in various settings, which enhances the generalizability of the results. Lastly, the study may increase the knowledge of how the structure, content and follow-up of rehabilitation stays can contribute in optimizing the effect of such stays. If proven effective, the programme may also be applied within other fields of rehabilitation, as well as in less complex interventions directed at lifestyle changes and self-management.
